#### Secondary outcomes

All secondary outcomes will be compared between the PR and usual care arms from baseline to 6-week and 12-week follow-ups.

Health questionnaires will be administered including COPD assessment test (CAT), Clinical COPD questionnaire (CCQ), Hospital Anxiety and Depression Scale (HADS), Patient Health Questionnaire (PHQ-9), Work Productivity and Activity Impairment (WPAI), and European Quality of Life 5-Dimensions (EQ-5D-5L). PR-specific measurements will include the ISWT, Endurance Shuttle Walking Test (ESWT), mid upper arm circumference and sit-to-stand test.

### Respiratory symptoms

The CCQ is a simple 10-time validated HRQoL questionnaire with good psychometric properties.^26^ It consists of 10 items, each scored between 0 and 6, divided into three domains (symptoms, functional, mental), with higher scores representing worse HRQoL. The CCQ is responsive to PR with an estimated minimal important improvement of 0.4.^27^

The CAT is a validated, self-administered, short and simple questionnaire that measures HRQoL.^28^ The CAT consists of eight items, each scored between 0 and 5 scored with a range of 0–40; scores of 0–10, 11–20, 21–30, 31–40 representing mild, moderate, severe or very severe negative impact on HRQoL, respectively. The CAT is responsive to the effects of PR with an estimated minimal clinically important difference (MCID) of 2 points.^29^

### Psychological well-being

The HADS questionnaire is a validated, easy to use screening tool for anxiety and depression symptoms in a hospital outpatient setting.^30^ The self-report rating scale is composed of 14 items with two 7-item subscales (HADS-Anxiety and HADS-Depression), both ranging from 0 to 21 with higher scores indicating more severe distress. The HADS is responsive to PR with estimated MCID of 2 points on each subscale.^31 32^

The PHQ-9 is a nine item, validated, short, self-administered and positively worded questionnaire designed to measure the severity of depression over the last 2 weeks.^33^ The total score ranges from 0 to 27, with high scores indicating high depression, specifically; no depression (0–4), mild (5–9), moderate (10–14), moderately severe (15–19) or severe depression.^20–27 33^ The PHQ-9 has an estimated MCID of 5 points.^34^

### Work productivity and impairment

The WPAI questionnaire is a validated instrument to measure impairments in work and activities, both paid and unpaid. The WPAI self-administered questionnaire measures time missed from work, impairment of work and regular activities due to overall health and symptoms, during the past 7 days.^35^ We have added two follow-up supplementary questions, following the WPAI format, to measure productivity with respect to regular household duties in low-resource settings.

### Health-related quality of life

The EQ-5D-5L questionnaire is a standardised questionnaire, developed to measure of health outcomes and defines health in terms of five dimensions: mobility, self-care, usual activities, pain or discomfort and anxiety or depression.^36^ The questionnaire also contains a visual analogue scale. The EQ-5D-5L will be used to calculate patient costs per quality-adjusted life-year. EQ-5D-5L is responsive to change following PR, with a MCID of 0.05 (utility index) and 7.0 (Visual Analogue Scale).^37^

### Exercise capacity/ physical function

The five-repetition sit-to-stand test (FTSTS) is a commonly used functional performance measure of lower-limb strength.^38^ The FTSTS measures the time taken to stand five times from a sitting position as rapidly as possible. The FTSTS is reliable, valid and responsive to PR with an estimated MCID of 1.7 s.^39^

The MRC dyspnoea scale is a 5-point self-administered questionnaire based on the sensation of breathing difficulty experienced by the patient during daily life activities. The questionnaire is short, easy to use and has grades ranging from 1 (none) to 5 (almost compete incapacity), with high grades indicating high perceived respiratory disability.^40^ The MRC dyspnoea scale is responsive to PR with estimated MCID of 1 points.^41 42^

The ESWT is a constant-load exercise test which measures the ability of the participant to sustain a given submaximal exercise capacity; the participant aims to walk at 85% of their maximal ISWT walking speed.^23^ The ESWT is frequently used as an exercise tolerance outcome measure for PR. The endpoint of the test is the time the participant walks at the constant endurance speed. The test consists of prerecorded audio signals at different frequencies giving a total of 16 walking speeds. The ESWT is responsive to PR with MCID following a 6 week PR programme between 174 and 279 s.^43^

### Physical activity

Participants will be asked to wear an ActiGraph wGT3X-BT activity monitor (ActiGraph, Pensacola, Florida, USA), able to detect a range of PA intensities.^44^ Participants will be instructed to wear the PA monitor on the right anterior hip during waking hours for 1 week prior to attending PR (preintervention) and for 1 week prior to their postintervention assessment (online supplemental table 2). Written instructions to follow will be provided to the participants prior to wearing and using the PA monitors.

10.1136/bmjopen-2020-047641.supp2Supplementary data

### Cost/benefit analysis

The cost of starting and running a PR programme will include single and recurrent costs (table 2). Single payments will include the necessary costs needed to set up and run PR. Recurrent costs refer to any item with a life expectancy of ≤1 year (eg, disposable materials).^45^ The fixed costs will be captured prior to enrolling the first participant into the PR programme and the recurrent costs will be collected at the mid-stage of recruitment. The average fixed and recurrent costs will be calculated separately.

**Table 2 T2:** Table showing the variables used to calculate fixed and recurrent costs (not an exhaustive list)

Fixed costs	Recurrent costs
Electrical equipment (laptop, printer, projector) Equipment for PR (weights, treadmill, cycle ergometer, country-specific equipment, step-up box, chairs) Equipment for shuttle walking tests (cones, licences, stop watches, tape measure, electrical equipment to play audio) Equipment for PR assessment (height stadiometer, weight scales, sphygmomanometer, pulse oximeter, spirometer, calibration syringe, country-specific equipment) Additional safety equipment (blood glucose monitor, oxygen cylinder holder) Miscellaneous (filing cabinets, storage units, questionnaire translations, questionnaire licences, staff uniform) Staff time (creating core PR content including educational material, exercise diaries and other necessary paperwork)	Staff time to conduct PR (assessment at baseline and discharge, conduct PR classes, telephone calls and data entry) Disposable equipment (for blood glucose monitor, spirometer mouthpieces, nose-clips) Servicing costs (spirometer, PR equipment, specifically cycle ergometers) Miscellaneous (oxygen cylinders, questionnaire licences, stationery (paper) Patient costs (transport and meals)

PR, pulmonary rehabilitation.

### Patient and public involvement

Adults with CRDs tell us how they are greatly troubled by breathlessness and express interest in attending a programme that can help better manage their condition. They express interest in attending a hospital-based programme that allows them to interact with fellow patients. They additionally tell us how the PR programme should be delivered. We have also set up a patient and public involvement group at MLI that will meet regularly, and assist with disseminating results following the study.

### Data analysis

All randomised participants will be included in the intention to treat analysis population. The primary efficacy analysis will be based on both per protocol and modified intention-to-treat populations. For the primary analysis, the differences in the primary outcome (walking distance on the ISWT) with the corresponding two-sided 95% CI and p value will be estimated using a stratified analysis; a p<0.05 will be the measure for statistical significance. Predictive analytics software (SPSS^16^) will be used to analyse the data. Continuous data will be presented as mean and SD or median and IQRs, while categorical data will be presented as frequencies and percentages. All data will be assessed for normality and appropriate parametric and non-parametric tests will be used. Categorical variables between the two treatment groups will be compared using χ^2^ and Fisher’s exact test as appropriate. Continuous variables will be compared using t-test for normally distributed data and Mann-Whitney-U test for non-normally distributed data. Any baseline differences will be adjusted for. Both intention-to-treat and per-protocol analyses will be conducted after imputing any missing data. There will be no formal interim analysis of data. The final analysis will be performed when all the 114 participants have completed the last study related visit or previously withdrawn from the trial. We will fit linear mixed models for both per-protocol and intention-to-treat analyses.

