**Methods and analysis:**

This is a randomised waiting-list controlled trial with blinded outcome measures, comparing PR versus usual care for patients with PTBLD. A total of 114 participants will be randomised (1:1) to receive either usual care (on the waiting list) or PR, with follow-up assessments at 6 weeks and 12 weeks postintervention. The primary outcome is change in walking distance measured by the Incremental Shuttle Walk Test from baseline to the end of 6 weeks of PR. All secondary outcomes will be compared between the PR and usual care arms from baseline to 6-week and 12-week follow-ups. Secondary outcomes include self-reported respiratory symptoms, physical activity, psychological well-being, health-related quality of life and cost–benefit analysis. All randomised participants will be included in the intention-to-treat analysis population. The primary efficacy analysis will be based on both per-protocol and modified intention-to-treat populations.

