### Sample size

The study will be powered to detect a 35 m difference in the ISWT measured at baseline and after completion of PR.^18^ Assuming that ISWT follows an approximately normal distribution, a power calculation based on a paired t-test was performed. Based on a trial sample size of 40 participants in each of the treatment and control groups, a two-sided 5% significance level and a statistical power of 80%, the clinically important change in ISWT of 35 m will also be statistically significant. Our recent feasibility study^15^ was used to obtain an estimate of the pooled SD for the power calculation. Conservatively assuming up to 30% losts to follow-up at 6 weeks, a total of 114 participants are required to be recruited and randomised (1:1) to each arm (PR: 57 participants or waiting list: 57 participants). Using the 70% ineligibility rate during screening from the feasibility study, we will need to screen approximately 543 PTBLD patients.

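### The primary efficacy analysis is assigned to two unranked populations, per-protocol and modified ITT, and the section contradicts itself on which set carries the primary result

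*Protocol article*

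**What the plan says.** The Data analysis section of the protocol article first defines a full set: "All randomised participants will be included in the intention to treat analysis population". The next sentence gives the primary result to other sets: "The primary efficacy analysis will be based on both per protocol and modified intention-to-treat populations". The abstract, under Methods and analysis, repeats it: "The primary efficacy analysis will be based on both per-protocol and modified intention-to-treat populations".

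Later in Data analysis, the modified ITT set is no longer mentioned and the full ITT set returns. On missing data: "Both intention-to-treat and per-protocol analyses will be conducted after imputing any missing data". On the model: "We will fit linear mixed models for both per-protocol and intention-to-treat analyses".

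One threshold is given for the primary analysis, "a p<0.05 will be the measure for statistical significance". The text does not say which population it applies to, or whether one or both results must meet it.

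**The concern.** Three populations are named, and the two that carry the primary label do not include the one made up of all randomised participants. Without a ranking or a rule for disagreement, a reader of the results cannot tell which estimate was meant to decide the trial, and either could be presented as primary.

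The per-protocol set is the more serious part. The trial compares PR with usual care for superiority and describes itself as a pragmatic effectiveness trial. It has no non-inferiority aim, which is the usual reason for giving a per-protocol analysis co-primary standing. PR means 12 supervised hospital sessions over 6 weeks, while the control arm waits. Exclusions for poor attendance at sessions can therefore arise only in the PR arm. If those who complete the programme are fitter or more motivated, the groups compared are no longer the groups randomised, and part of that difference would be credited to PR. Blinded outcome assessment does not remove this.

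**Working it through.** **Text side by side**

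| Place | Sets named | Purpose |
|---|---|---|
| Abstract, Methods and analysis | per-protocol, modified ITT | primary efficacy |
| Data analysis, opening | ITT = all randomised | definition |
| Data analysis, next sentence | per-protocol, modified ITT | primary efficacy |
| Data analysis, later | ITT, per-protocol | imputation |
| Data analysis, end | per-protocol, ITT | linear mixed models |

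Nothing elsewhere in the article ranks the sets or makes ITT primary.

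**Inputs from the Sample size section:** 40 evaluable per arm, 35 m difference, two-sided 5% level, 80% power, up to 30% loss. No SD is given.

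**The plan's own figure.** 40/(1 − 0.30) = 57.1 per arm and 80/0.70 = 114.3 in total. The stated 57 per arm and 114 are reproduced.

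**SD implied by the plan.** For a two-sample comparison, SD = 35 / [(1.960 + 0.842) × √(2/40)] = 55.9 m, or 55.2 m with the t distribution. I use about 55 m below.

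**Illustration 1: selection bias with no true effect.** Assume that only the PR arm is trimmed, that its least adherent 30% are dropped, and that adherence has correlation r with ISWT change under bivariate normality.
- Bias in SD units = r × φ(z₀.₃₀)/(1 − 0.30). With z₀.₃₀ = −0.524 and φ = 0.348, this is r × 0.497.
- r = 0.2: 0.10 SD, about 5.5 m.
- r = 0.4: 0.20 SD, about 11 m, which is a little under a third of 35 m (11/35 = 0.31).

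**Illustration 2: two tests with the same exclusion.** Take modified ITT as 40 versus 40, and per-protocol as 28 versus 40 (40 × 0.70 = 28).
- Information fraction = (1/40 + 1/40)/(1/28 + 1/40) = 0.0500/0.0607 = 0.82.
- Correlation of the two test statistics = √0.82 = 0.91.
- Under no effect, and leaving out the bias in illustration 1, the bivariate normal probability that at least one test has p<0.05 is about 7.0%.
- The probability that both do is 5% + 5% − 7.0% = about 3.0%, below the nominal 5%.

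**After the fix.** One test in one population has a type I error of 5%, and the 114 does not change.

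**The case against.** The strongest reply has four parts.

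*Definitions may lie elsewhere.* The article defines neither per-protocol nor modified ITT, and a full protocol or SAP commonly does. This stands: their absence is not part of the point, and a comparison of PR completers with all controls is an assumption. Controls must also attend the assessment visits at 6 and 12 weeks (Assessment and follow-up), so they too can be excluded. But only the PR arm has sessions to miss, so the likely direction remains. An SAP that made ITT primary would contradict this published sentence.

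*An all-randomised analysis is already planned.* It is, with imputation and mixed models, and this limits the harm. It is not labelled primary, however, and its presence beside the primary sentence creates the contradiction.

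*Modified ITT may be harmless.* It may mean only participants with a post-baseline walk test, which need not depend on sessions attended. This stands. No bias mechanism for modified ITT can be shown from the article, and a full ITT result with up to 30% loss leans heavily on imputation.

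*The word "both" may mean that both must succeed.* That reading is at least as natural as the alternative and does not inflate type I error. The article does not state it, and the bias in the per-protocol estimate would remain.

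Two stronger readings are tempting. A reader might infer that the plan as written inflates the false-positive rate; this follows only from an either-result rule that the article never states. A reader might also infer a large loss of power if both are required. For illustration 2 with equal true effects, joint power is about 70%. Once the bias in illustration 1 is included, it is about 77 to 80%, close to the planned 80%. The two harms largely offset and should not be added together.

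**Conclusion.** The point holds. The article fixes two unranked primary populations, one of them per-protocol, in a superiority effectiveness trial, and is inconsistent between modified ITT and ITT. That leaves the main conclusion open to selection bias, probably favouring PR, and to a choice between results.

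The defect rests on the text alone. Its size does not: the article gives no SD, adherence rate, adherence-outcome correlation or per-protocol rule. The 5.5 to 11 m and the 7.0% are illustrations under the stated assumptions, and the 7.0% applies only if either result may be claimed.

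A reader who takes the paired t-test named under Sample size literally could solve back to an SD of 77 m and infer a bias of about 15 m, or 44% of the 35 m target (0.199 × 77 = 15.3; 15.3/35 = 0.44). I do not put that forward. An SD of that order does not fit 80% power for a comparison between arms of 40: at 79.0 m, the normal-approximation version of the same figure, that power is about 51%.

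**What to change.** In the abstract and in Data analysis, name one primary analysis: all randomised participants in the arm assigned, regardless of sessions attended. This is the ITT analysis already planned. Make per-protocol, and modified ITT if it is kept, supportive, with no role in the primary conclusion. Use the same population names in the imputation and mixed-model sentences. Do this before results by arm are seen.

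The cost is wording only, and the sample size of 114 is unchanged. The downside is that the headline estimate may be somewhat smaller than a per-protocol one and will rely on the planned handling of missing data, with up to 30% loss assumed at 6 weeks.

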### Randomisation

Once eligible participants have consented to take part in the study, they will be randomised using a web-based randomisation system (https://www.sealedenvelope.com/). Participants will be randomised (1:1) to receive either usual care or PR. Access to the web-based system will be controlled through an authorised username and password. Randomisations will be conducted by a member of the study team independent from the data collection team and will be revealed to the data collection and intervention delivery teams after baseline measurements have been obtained.

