### Study outcomes

#### Primary outcome

The primary outcome is change in walking distance measured by the ISWT from preintervention to postintervention. A group change of at least 35 m is considered clinically important.^18^

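### The article does not say which of several methods, in which population, gives the primary ISWT p value, and it lets chance imbalance choose the covariates instead of always adjusting for baseline ISWT

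*Protocol article*

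**What the plan says.** All of the following comes from the Data analysis section of the protocol article unless another section is named.

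- **Endpoint (Primary outcome section).** "The primary outcome is change in walking distance measured by the ISWT from preintervention to postintervention". A group change of 35 m is taken as clinically important.
- **Method tied to the primary outcome.** The ISWT difference, its two-sided 95% CI and p value "will be estimated using a stratified analysis; a p<0.05 will be the measure for statistical significance".
- **Rule for continuous variables.** "All data will be assessed for normality and appropriate parametric and non-parametric tests will be used", and then "Continuous variables will be compared using t-test for normally distributed data and Mann-Whitney-U test for non-normally distributed data".
- **Models.** The section closes with "We will fit linear mixed models for both per-protocol and intention-to-treat analyses".
- **Covariates.** "Any baseline differences will be adjusted for". No covariate is named.
- **Missing data.** "Both intention-to-treat and per-protocol analyses will be conducted after imputing any missing data". No imputation method is named.
- **Populations.** All randomised participants form the intention-to-treat set, but the primary efficacy analysis is placed in both a per-protocol and a modified intention-to-treat set.
- **Allocation (Randomisation section).** "Participants will be randomised (1:1) to receive either usual care or PR". No stratification factor is mentioned.

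**The concern.** A primary analysis should be one estimate, in one population, from one method fixed before the data are seen. Here a reader cannot tell which result is held to p<0.05. ISWT distance is continuous, so the t-test or Mann-Whitney rule covers it on its wording. The mixed-model sentence has no outcome limit either. The stratified analysis, the only method attached to ISWT by name, cannot be carried out from the text because its strata are not given.

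Two of the stated rules are also poor choices in themselves:

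- If the normality check leads to Mann-Whitney, that test gives no mean difference in metres to compare with 35 m.
- Adjusting for whatever differs at baseline lets chance pick the covariates. Baseline ISWT is measured before randomisation in every participant (Table 1) and is an obvious predictor of ISWT at 6 weeks, yet it is not fixed as a covariate.

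At stake are a primary result that is open to choice after the data are seen, and precision that would cost nothing to obtain.

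**Working it through.** **1. The sentences side by side**

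| Statement | Applies to ISWT by | Yields |
|---|---|---|
| Stratified analysis | name | difference, CI and p; strata unknown |
| t-test if normal | general wording | mean difference |
| Mann-Whitney if not normal | general wording | rank comparison, no mean difference in metres |
| Linear mixed models | general wording | difference by visit, depending on terms not listed |

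The populations do not line up either. The primary sentence uses per-protocol and modified intention-to-treat; the imputation and mixed-model sentences use per-protocol and intention-to-treat.

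**2. The plan's own figure**

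Inputs from Sample size: 40 evaluable per arm, 30% loss, 35 m, two-sided 5%, 80% power.

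40 / (1 − 0.30) = 57.1, or 57 per arm and 114 in total. The stated total is reproduced (rounding up would give 58 per arm, 116 in total). The 40 per arm cannot be checked forward because no SD is given, so it is solved backward.

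**3. SD implied by 40 per arm**

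- Two-sample comparison: SD of change = 35 / [(1.960 + 0.842) × √(2/40)] = 35 / (2.802 × 0.2236) = 55.9 m (55.2 m with the t distribution).
- Paired t-test on 40 people, which is the test the article names: SD of change = 77.0 m, solved with the t distribution.

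**4. Power with baseline ISWT always in the model**

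Assumptions: equal variance at baseline and follow-up, and baseline-to-follow-up correlation r between 0.5 and 0.9. The article gives no r.

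Adjusted SD = SD of change × √[(1 + r)/2]

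Power = Φ(35 / [SD × √(2/40)] − 1.960), with 40 per arm

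| | SD of change 55.9 m | SD of change 77.0 m |
|---|---|---|
| Unadjusted change | 80% | 53% |
| r = 0.5 (factor 0.866) | SD 48.4, power 89.9% | SD 66.7, power 65.0% |
| r = 0.7 (factor 0.922) | SD 51.5, power 86.0% | SD 71.0, power 59.6% |
| r = 0.9 (factor 0.975) | SD 54.5, power 82.0% | SD 75.1, power 54.9% |

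**5. What the triggered adjustment does**

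The article does not say how a baseline difference is judged; a 5% test is assumed. Under randomisation such a test is positive in about 1 trial in 20, so baseline ISWT would enter the model in only about 5% of trials and the gain in step 4 would mostly be lost.

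Simulated rejection rates under no effect, at a nominal 5% with 40 observed per arm:

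| Rule | Rejection rate |
|---|---|
| One fixed baseline-adjusted model | 4.8–5.3% |
| Follow-up comparison, adjusted only when baseline differs | 3.4–4.9% |
| Normality check, then t-test or Mann-Whitney on change, normal data | 5.0–5.5% |
| The same, lognormal data | 4.5–5.1% |
| Normality switch plus triggered adjustment | 4.2–5.0% |

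The written rules therefore lose efficiency; they do not raise the false-positive rate materially.

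**The case against.** The sponsor could fairly say that this is a condensed article. Only the stratified analysis is attached to ISWT by name. The t-test and Mann-Whitney sentence stands beside descriptive statistics and chi-square rules, and may be meant for baseline and secondary variables. The mixed model may be how the stratified primary analysis is carried out, and may already contain baseline ISWT. The full protocol may name the strata.

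Much of this stands. The methods are unreconciled rather than incompatible, and silence in the Randomisation section does not show that allocation was unstratified. What does not fall away is that the text, as written, states several methods and two primary populations without ranking them, and sets a covariate rule that is worse than fixed adjustment. An analysis plan naming a single model would have to overrule this text.

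Three stronger readings are tempting and are not supported:

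- **Inflated type I error from several available tests.** That requires someone to report the smallest p value. The article selects the test by normality, and the rule as written holds close to 5%.
- **Inflated type I error from imputation.** That requires single imputation with filled-in values treated as observed. The article names no method, and properly pooled multiple imputation before a mixed model is valid. It can also draw on measurements outside the model, so it is not pointless.
- **A definite power gain.** The rise from 80% rests on a back-solved SD and an assumed correlation.

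**Conclusion.** The point holds in this form: the primary ISWT comparison has unreconciled methods and two primary populations, and the covariate rule gives up precision that fixed baseline adjustment would provide at no cost.

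At 40 per arm, fixed adjustment raises power from 80% to about 90% (r = 0.5) or 82% (r = 0.9) if the unstated SD of change is about 56 m. If it is about 77 m, the rise is from about 53% to 65% or 55%, and adjustment does not rescue the trial's power. That second case is a question for the sample-size section, which should state its SD and use a between-arm calculation. Both ranges assume equal variances and r between 0.5 and 0.9.

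The ambiguity leaves room for choice after the data are seen, but no specific type I error inflation follows from the written plan.

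**What to change.** Name one primary analysis in one primary population:

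- **Model.** A linear mixed model of ISWT at 6 and 12 weeks with arm, visit, arm-by-visit and baseline ISWT, the last always included.
- **Strata.** Add any factors actually used to stratify randomisation and name them. If there were none, remove the word stratified.
- **Primary estimate.** The adjusted 6-week difference in means, in metres, with 95% CI and p value.
- **Population.** Choose one for the primary p value and label the others supportive.
- **Remove for this outcome** the normality-driven switch of test and the rule of adjusting for observed baseline differences.
- **Missing data.** Either fit the likelihood-based mixed model to the observed data, or use multiple imputation with pooled standard errors. Both are valid under missing at random. Do not treat singly imputed values as observed. With up to 30% loss allowed for, add a sensitivity analysis to that assumption.

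The cost is wording in the protocol and analysis plan, settled before the outcome data are seen. No new data or participants are needed for this change.
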